### Trial stopping rules

The trial may be interrupted or terminated early if there are sufficient and reasonable grounds. Situations justifying termination or interruption include unexpected serious AEs as determined by the Ethics Review Committee. If an AE does occur, the research team will evaluate and record the nature, duration, severity, course, and relationship to the participant and the trial. This information will be reported immediately to the Kurashiki Heisei Hospital Ethics Review Committee, which will then decide whether to continue, modify, or terminate the study. Furthermore, even if subject recruitment is still incomplete, the trial may be terminated early based on the judgment of the Ethics Review Committee and the principal investigator.

### Research ethics approval, protocol amendments, and consent or assent

This trial has been approved by the Ethics Review Committee of Kurashiki Heisei Hospital (R07‐009). Additionally, this trial has been registered with the University Hospital Medical Information Network (UMIN) (UMIN000058947). For reasons such as research objectives or study design, should any protocol amendments be necessary, the principal investigator (with co‐investigators' consent) shall submit amendments to the Ethics Review Committee for approval. As required before implementation, electronic informed consent will be obtained from all participants, via an online questionnaire, by clicking the button indicating agreement to participate. When obtaining informed consent, clearly explaining to participants the trial's potential risks and benefits is crucial—as is ensuring they fully understand them. Therefore, before obtaining electronic informed consent, researchers will provide a written explanation of the potential risks and benefits of participating in the study, the content of the intervention (including that subliminal words such as “can” and “let us try” are displayed during the video), the assessments to be used, and the right to withdraw from participation at any time. Additionally, researchers will inform participants that participation is voluntary and that they may withdraw at any time.

### Dissemination policy

This trial will be submitted to an international peer‐reviewed journal regardless of whether the clinical hypothesis yields positive or negative results. Furthermore, we will promote wider dissemination by posting the trial overview and results on the hospital's website and by participating in and presenting at several domestic and international conferences.

## DISCUSSION

As a precursor to MDD, StD causes problems that can include decreased daily activities, reduced quality of life, worsening health status, increased economic costs, and increased mortality.^3^, ^5^, ^6^, ^7^, ^8^, ^9^, ^10^ Particularly important, however, is that StD is a risk factor for MDD.^1^, ^2^, ^6^ If effective interventions for depressive symptoms in individuals with StD are established, they could not only help maintain patients' mental well‐being but also prevent MDD's onset. Among several effective interventions for StD, SPSRS represents a groundbreaking, novel strategy: a video‐viewing website to reduce depressive symptoms.^11^, ^12^, ^16^, ^81^ The pilot RCT suggested that SPSRS can potentially improve depressive symptoms in individuals with StD.^25^ If this study replicates SPSRS's efficacy for depressive symptoms, considering its advantages (free access anywhere, ability to watch preferred videos), it could serve as an intervention for those who feel stigma about receiving psychotherapy or for individuals living in remote areas.^82^, ^83^, ^84^, ^85^ This would contribute to meeting current mental‐health needs by accommodating specific patient needs and preferences.^13^, ^14^, ^15^

As secondary outcomes in this trial, we established the K6 score for measuring psychological distress and the GAD‐7 score for measuring anxiety symptoms. Previous studies have suggested that factors influencing the transition from StD to MDD include not only depressive symptoms but also increased anxiety symptoms and psychological distress.^86^, ^87^, ^88^, ^89^ Considering that StD contributes not only to MDD but also to various other mental disorders' onset, if SPSRS also reduces psychological distress and anxiety symptoms, it could prevent not only the transition from StD to MDD but also to other mental disorders.^30^, ^90^ Despite this possibility, because the K6 and GAD‐7 scores were secondary outcomes, any observed intervention efficacy must be interpreted as preliminary. Should significant intervention efficacy be found for K6 or GAD‐7 scores, a new trial with these measures as primary outcomes would be necessary.

A previous systematic review suggested that RCTs for evaluating medical devices' efficacy (including mobile health applications) must adequately address trial design barriers, for example, randomization, participant acceptance and compliance, blinding, and determination of appropriate outcome measures.^91^, ^92^ Trials should also be carefully designed to minimize the risk of bias. Considering the Medical Research Council's methodological framework, therefore, we will evaluate SPSRS's efficacy on depressive symptoms in individuals with StD through several trials conducted in accordance with rigorous scientific methods.^93^

To minimize risk of bias, we designed this trial to address previous SPSRS studies' issues and limitations as well as their benefits. But even this trial is not without limitations. First, it was conducted exclusively with native Japanese speakers, so the results cannot be generalized across countries or cultural backgrounds. Second, the trial was conducted with individuals with no history of mental illness; therefore, its results may not apply to individuals with StD who do have a history of mental illness. Third, participants in the waiting‐list control group who wish to receive the SPSRS intervention will receive it after 5 weeks and completion of the assessment questionnaire. Although the waiting‐list control group allows us to verify SPSRS efficacy properly, we cannot entirely rule out the possibility that the waiting‐list control group's expectations or disappointment may influence the results. Fourth, this trial did not include a follow‐up assessment, so whether any efficacy persists after the intervention remains unclear. Fifth, participants will be assessed for MDD prior to the trial using the PHQ‐9 rather than a structured interview such as the MINI. Therefore, individuals with mild MDD (rather than StD) may be included as participants. Sixth, considering the burdens imposed by study participation, no follow‐up is planned after the intervention. Therefore, even if the 5‐week SPSRS intervention proves effective for depressive symptoms in individuals with StD, it remains unclear whether the therapeutic effect will persist. Previous studies have suggested that individuals with StD frequently progress to MDD 1–3 years after baseline assessment.^39^, ^94^ Therefore, future trials should include longer term follow‐up (e.g., 1–3 years) to investigate whether the therapeutic effects of SPSRS on StD symptoms are maintained and whether the intervention reduces the risk of future MDD onset. Seventh, participants for this study will be recruited via an online survey from a panel list maintained by a market research company. Therefore, the potential pool of participants will be restricted, which could introduce selection bias limiting the generalizability of the results, such as for demographic subgroups under‐represented in these panels. Eighth, we will be unable to provide mental‐health resources to candidates reporting suicidal ideation on the PHQ‐9 due to the market research company's privacy policy and terms of use. Therefore, as reported in previous studies using internet surveys, implementing best practices for addressing risks such as suicidal ideation may be difficult.^95^, ^96^ Instead, we plan to provide information on mental‐health resources upon request from participants, as simply enquiring about suicidal ideation is very unlikely to increase the risk of suicide attempt.^97^, ^98^ Nonetheless, the restriction on proactive intervention is one of the major limitations of the present trial, and future studies employing similar methodologies should seek technical solutions that incorporate real‐time safety measures without compromising anonymity. Finally, due to the intervention's nature, blinding intervention providers and participants was too difficult, so that inability might introduce performance bias, potentially skewing results in the intervention group's favor.

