#### Exclusion criteria

(1)Individuals with a lifetime history of mental illness.(2)Individuals receiving treatment from mental‐health professionals.(3)Persons with visual or hearing impairments that adversely affect their daily lives.(4)PHQ‐9 Item 1 (Little interest or pleasure in doing things) or Item 2 (Feeling down, depressed, or hopeless) with responses of “several days,” “more than half the days,” or “nearly every day,” and who also responded “more than half the days” or “nearly every day” to five of nine items.^39^

Generally, StD does not meet diagnostic criteria for MDD but is considered present when an individual experiences clinically significant depressive symptoms as measured by PRO.^3^ However, because a market research company will conduct this trial, ruling out MDD based on structured interviews such as the Mini‐International Neuropsychiatric Interview (MIINI) will be difficult.^40^ In such cases, one approach is to use the PRO Depression Scale to rule out MDD.^39^, ^41^, ^42^, ^43^, ^44^, ^45^ In a previous study, individuals were judged to have MDD if, in addition to having a CES‐D score of 16 or higher, they responded “several days,” “more than half the days,” or “nearly every day” to PHQ‐9 Item 1 (Little interest or pleasure in doing things) or Item 2 (Feeling down, depressed, or hopeless), and responded “more than half the days” or “nearly every day” to five or more of the nine items.^39^ In contrast, those with a CES‐D score of 16 or higher who did not meet the PHQ‐9 criteria for MDD were judged to have StD.^39^ In this trial, StD is defined according to the identification method used in the previous study.

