### Study setting and recruitment timeline

This trial will recruit participants from the panel network (36 million members) of a Japanese market research company (Macromill Group, Tokyo) from October 1, 2025, to March 31, 2030. The research firm will email invitations to panelists aged 18–64, explaining the trial's purpose and procedures. The invitation will include an electronic consent option; individuals who check “consent” will be deemed to have agreed to participate in the main trial and can proceed to the online questionnaire for eligibility assessment. Participants who meet eligibility criteria will then undergo a baseline assessment and be considered enrolled. By the Central Registration Center at Kagoshima University, they will subsequently be randomly assigned to the experimental or the waiting‐list control group. Participants will be scheduled to complete Japanese versions of the CES‐D, Kessler Screening Scale for Psychological Distress (K‐6), and Generalized Anxiety Disorder‐7 (GAD‐7) questionnaires at 3 and 5 weeks after the intervention begins.^31^, ^46^, ^47^, ^48^, ^49^ Additionally, at 5 weeks after the intervention begins, the Global Rating of Change (GRC) scales will be assessed in addition to the CES‐D, K6, and GAD‐7.^50^, ^51^ The CES‐D will be administered during the main trial's eligibility assessment, while the K6 and GAD‐7 will be administered during baseline assessment. At 3 weeks after the intervention begins, assessments will be conducted in the following order: CES‐D, K6, and GAD‐7. At 5 weeks, assessments will be conducted in the following order: CES‐D, K6, GAD‐7, and GRC scales. Demographic information and lifestyle characteristics will be assessed only at baseline. Figure 1 shows the study's flowchart, and Table 1 shows the assessment schedule.

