### Adverse events and post‐trial care

Multiple studies have examined SPSRS as a treatment for StD using the same 5‐week intervention period, and none have reported serious AEs, such as the onset of MDD.^16^, ^24^, ^25^, ^29^ Nonetheless, the possibility of such adverse effects on participants' physical and mental health should never be discounted during clinical trials. Therefore, we will employ methods similar to those used in previous studies to systematically monitor the occurrence and signs of AEs and respond promptly.^24^, ^80^ AEs are considered signs of deteriorating mental or physical health, regardless of whether the individual participates in the SPSRS‐based intervention. Participants will be encouraged to consult with the chief investigator if they notice any signs of deterioration in their mental or physical health during or after the trial. Furthermore, monitoring for serious AEs will continue after trial completion. To ensure prompt and appropriate handling of AEs occurring after trial completion, participants may contact the research team for up to one month after the final survey. This information will be conveyed to each participant during the electronic informed consent process. If an AE is reported, the research team will evaluate and document the nature, duration, severity, and outcome, as well as the participant's relationship to the study. Any AEs will be immediately reported to the Kurashiki Heisei Hospital Ethics Review Committee, which will decide whether the study should be continued, modified, or discontinued. Additionally, the research team will contact all participants and strongly recommend that they utilize relevant health services and consult mental health professionals if needed. Medical expenses related to AEs will not be covered as harm beyond that typically associated with the care provided in this trial is considered extremely unlikely.

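### The eligibility PHQ-9 records suicidal ideation without excluding on it, yet resource information is planned only on request, and the stated reasons do not rule out giving the same text to everyone

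*Protocol article*

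**What the plan says.** All references are to the protocol article.

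- **Exclusion criteria, item 4.** A candidate is excluded if PHQ-9 item 1 or 2 scores at least 1 and the person is also one "who also responded “more than half the days” or “nearly every day” to five of nine items". No single item excludes on its own.
- **Discussion, eighth limitation.** The authors state that "we will be unable to provide mental‐health resources to candidates reporting suicidal ideation on the PHQ‐9", citing the panel company's privacy policy and terms. In its place "we plan to provide information on mental‐health resources upon request from participants", with the justification "as simply enquiring about suicidal ideation is very unlikely to increase the risk of suicide attempt". They call the restriction a major limitation.
- **Adverse events and post-trial care.** Participants are encouraged to consult the chief investigator if they notice their mental or physical health getting worse. Contact stays open for up to one month after the final survey, and each participant is told this in the electronic consent process. In the sequence that follows a reported adverse event, "the research team will contact all participants and strongly recommend that they utilize relevant health services and consult mental health professionals if needed".
- **Study setting and recruitment timeline.** "The invitation will include an electronic consent option", and the eligibility questionnaire comes after consent. The week-3 survey holds CES-D, K6 and GAD-7. "At 5 weeks, assessments will be conducted in the following order: CES‐D, K6, GAD‐7, and GRC scales". The PHQ-9 is not scheduled again.
- **Research ethics approval, protocol amendments, and consent or assent.** "before obtaining electronic informed consent, researchers will provide a written explanation of the potential risks and benefits of participating in the study".

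**The concern.** The trial asks people with raised depressive symptoms about suicidal ideation, can randomise those who report it (half of them to five weeks of waiting), and plans to give resource information when someone asks for it. Exclusions 1 and 2 remove people with a history of mental illness or in current mental-health treatment. An enrolled person who reports ideation is therefore, by design, not under a mental-health professional's care at entry.

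The constraint that the article cites concerns acting on one person's answer. Fixed text shown to every candidate uses no answer and identifies no one, so that constraint as stated does not reach it. What is at stake is participant safety, not inference.

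**Working it through.** The plan gives no figure on this point, so there is none to reproduce. The check has four parts.

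**1. Does exclusion 4 remove people who report ideation?** The rule is: (item 1 ≥ 1 or item 2 ≥ 1) and at least five of nine items ≥ 2, each item scored 0 to 3. The article names items 1 and 2 as interest and mood, so ideation is taken to be one of the other seven. Fix the ideation item and count the 4^8 = 65,536 patterns of the other eight. Each item has two values below 2 and two values at 2 or above.

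- *Ideation item at 3.* Not excluded if at most three of the other eight are ≥ 2: 2^8 × (1 + 8 + 28 + 56) = 256 × 93 = 23,808. Also not excluded if items 1 and 2 are both 0 and at least four of the remaining six are ≥ 2: 2^6 × (15 + 6 + 1) = 1,408. Total 25,216 of 65,536, or 38.5%.
- *Ideation item at 1.* At most four of the other eight ≥ 2: 256 × (93 + 70) = 41,728. Items 1 and 2 both 0 with at least five of six ≥ 2: 64 × (6 + 1) = 448. Total 42,176 of 65,536, or 64.4%.
- *Example.* Items 1, 2, 3 and the ideation item at 3, the other five at 1. Four items are ≥ 2 and the total is 4 × 3 + 5 × 1 = 17. The rule does not exclude this person.

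These are counts of response patterns, not prevalences, and CES-D ≥ 16 and the other criteria still apply. They show only that the rule does not screen ideation out.

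**2. Do the two stated reasons support waiting for a request?**

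- The company's terms are cited for candidates who report ideation. That covers singling out a person by an answer. It does not cover text that is the same for all.
- The low risk from enquiring defends asking the question. It does not bear on what someone who already has ideation should be given.

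**3. What else reaches participants?**

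| Stated step | What starts it | Resource list? | Triggered by a PHQ-9 answer? |
|---|---|---|---|
| Information on request (Discussion) | The person asks | Resource information | No |
| Invitation to consult the chief investigator, conveyed at consent | The person notices deterioration and makes contact | No | No |
| Recommendation of health services to all participants | A reported adverse event | No | No |

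The invitation is unsolicited and uniform. Because consent precedes the eligibility survey, candidates later screened out may also see it. It concerns worsening, whereas ideation at screening is a starting state.

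**4. Scale.** The documents give no rate of reported ideation. Assume a share p among the 400 randomised, 200 per arm (Sample size):

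| p (assumed) | Randomised, 400p | Expected on waiting list, 200p |
|---|---|---|
| 2% | 8 | 4 |
| 5% | 20 | 10 |
| 10% | 40 | 20 |
| 20% | 80 | 40 |

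Screened-out candidates would be additional and cannot be counted.

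**The case against.** The best reply is that the adverse-events section already has a universal message. Candidates learn at consent, before the PHQ-9, that they may contact the chief investigator, and resource information is available on request. This stands in part. A reader might infer that a person with ideation has no stated route to help, and the document does not support that. What remains is that the invitation is not a resource list, is framed around deterioration, and needs the person to act.

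Second, the consent pages are not shown and may already carry resource text, and the company's terms are also unseen and may bar survey-page notices. Both are possible. It would be wrong to say that the consent text lacks such a list, or that the company would permit one. The point rests on what the Discussion affirmatively states, an on-request plan, and the remedy is conditional on both unknowns.

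Third, the limitation is disclosed, the trial has ethics approval, and other care is unrestricted. All true, and there is no concealment. But the disclosure covers the restriction on proactive intervention. It does not say that untargeted text was considered or refused.

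Fourth, the range of 8 to 80 is not evidence. Agreed: exclusions 1 and 2 may well lower the share, and nothing in the argument depends on the range.

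**Conclusion.** The point holds in a limited form. The screen records ideation, exclusion 4 does not exclude on it, resource information is planned only on request, and neither stated reason explains why the same information cannot go to everyone. The two steps in the adverse-events section narrow the gap but do not close it: one depends on the person noticing deterioration and making contact, the other on an adverse-event report.

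The size in people is unknown. The 8 to 80 figure is an assumption for scale. No estimate, power or error rate changes. Confidence is medium, because the consent text and the company's terms are not available. The change is worth making because it is a safety gain at very low cost, not because the plan leaves participants without any provision.

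**What to change.** - Unless the consent text already does so, add a fixed list of mental-health resources to the written pre-consent message that every candidate sees, identical for all candidates and both arms.
- Where the panel company's terms allow, show the same list on the closing and screen-out pages of the eligibility survey, where the ideation item is asked.
- Keep the on-request route. Amend the eighth limitation in the Discussion to describe the universal text, or state there that the company refused it.

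**Cost.** A wording amendment, ethics committee approval, and confirmation from the panel company, including for text placed before consent, since the firm sends the invitation that carries the consent option. Recruitment was planned from October 1, 2025, so people screened before the amendment would not have seen the text. With recruitment planned to March 31, 2030, later candidates could still benefit. The text is the same in both arms and favours neither.

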
## CONCLUSION

This RCT investigated the efficacy of SPSRS, which presents positive word stimulation, on depressive symptoms in people with StD. If its hypotheses are supported, SPSRS is not only expected to be incorporated into routine clinical practice as an intervention strategy but may also help address contemporary mental‐health intervention issues.

## ETHICS APPROVAL STATEMENT

This trial has been approved by the Ethics Review Committee of Kurashiki Heisei Hospital (R07‐009).

## PATIENT CONSENT STATEMENT

As required before implementation, electronic informed consent will be obtained from all participants, via an online questionnaire, by clicking the button indicating agreement to participate.

## CLINICAL TRIAL REGISTRATION

August 31, 2025, https://center6.umin.ac.jp/cgi-bin/ctr/ctr_view_reg.cgi?recptno=R000067408. This study was registered with the UMIN (UMIN000058947) in Japan.

## Data Availability

Data sharing is not applicable to this article as no datasets were generated or analyzed during the current study.
